#### Statistical analysis

All data will be checked for normal distribution using the Kolmogorov test. For normally distributed data, continuous variables will be presented as mean ± SD and analyzed using the independent Student’s *t*-test. Nonnormally distributed data will be presented as the median and interquartile range (IQR) and compared using the Mann-Whitney U test where appropriate. Categorical data are presented as numbers (proportions, %) and will be analyzed using Fisher’s exact test or the chi-square test. For the study endpoints, 95% confidence intervals will be reported as appropriate to provide a more comprehensive understanding of the results.

The primary endpoint is the frequency of coughing episodes during the FFB operation period. If the primary endpoint adheres to a Poisson distribution or a negative binomial distribution, negative binomial regression is further utilized, adjusting for the influence of covariates [the severity classification of pneumonia, BMI, age, sex and operation time, baseline cough frequency (“occasional” or “frequent but stable”)]. If the primary endpoint conforms to a normal distribution, a multiple linear regression model is further adopted for the same covariate adjustment. Subgroup analyses for the primary endpoint will be performed according to age (<3 years old vs. ≥3 years old), sex (female vs. male), BMI (<15 vs. ≥15), operation type (BAL vs. BAL + airway mucosal biopsy vs. foreign body removal) and operation time (<20 min vs. ≥20 min). Recognizing the possibility of intra-observer variability in applying the cough threshold, we conducted a pre-specified sensitivity analysis for the primary endpoint. The frequency of coughing episodes will be re-calculated using two alternative, stricter definitions: “Worst-case” consolidation and “Best-case” granularity. The conclusions of the primary analysis are considered robust only if the between-group difference (rocuronium vs. normal saline) remained statistically significant (*p* < 0.05) in the same direction under both alternative sensitivity analysis scenarios.

The secondary endpoints will be analyzed using the multivariate logistic regression model or the generalized linear model, adjusting for the same covariates as those of the primary endpoint. Repeated measurement data will be analyzed using a mixed linear model to compare haemodynamic variables and cough scores in the PACU between groups. To address the issue of multiple comparisons for adverse events observed in secondary endpoints, the Benjamini-Hochberg procedure will be employed to control the false discovery rate.

The analysis will be performed on the modified intention-to-treat population. To ensure robustness, a per-protocol analysis will additionally be conducted; however, the intention-to-treat approach will remain the primary basis for analysis. Missing data will be processed by multiple imputation and maximum likelihood method. All endpoints are performed at the two-sided 5% significance level. Statistical analyses will be performed using SPSS statistics (version 19.0; IBM SPSS, Chicago, IL, USA).

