### Primary endpoint

The primary endpoint is the frequency of coughing episodes during FFB, calculated as the total number of coughing episodes divided by the procedure time. One coughing episode is defined as a period of continuous coughing that interferes with either adequate ventilation or procedural progress (1). Interference with ventilation is primarily identified by the main observer through real-time visual inspection of the capnography waveform and ventilator parameters. It is characterized by flattening or significant distortion of the capnography waveform for ≥3 s coincident with the cough or visible, sustained chest wall movement against the set ventilator cycle coincident with the cough. A concomitant decrease in SpO2 of ≥5% is a supportive but not mandatory criterion. Procedural interference refers to a situation where the bronchoscopist will verbally confirm any instance where coughing necessitates a deliberate pause in the advancement or manipulation of the bronchoscope to maintain visual clarity. A cough-free interval of at least 3 s between two consecutive coughs is considered as the criterion for distinguishing two separate coughing episodes.

Addressing the inherent challenge of precise chronometry during a dynamic procedure, the primary endpoint assessment will be conducted in real-time by a dedicated observer who is not engaged in other procedural tasks. This observer will receive training on the assessment protocol prior to the start of the trial to standardize recognition. The dedicated observer will also be trained to identify a distinct, perceptible pause in the coughing paroxysm, consistent with the approximate duration of 3 s, before recording a new episode. This method prioritizes clinical relevance and feasibility during an active procedure.

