### Secondary endpoints

The secondary endpoints are: (1) cumulative remifentanil dosage; (2) success rate of FFB operation; (3) hemodynamic variables; (4) cough scores in the PACU every 5 min; (5) procedure time defined as the duration from bronchoscope insertion to its removal; (6) discharge time which is defined as the interval from the removal of bronchoscopy until a modified Aldrete score of ≥9 is achieved; (7) adverse events that occur during the procedure and in the PACU, including desaturation (SpO_2_ < 90%) which is stratified into three categories: mild desaturation: 85% ≤ SpO2 < 90%, moderate desaturation: 80% ≤ SpO2 < 85%, severe desaturation: SpO2 < 80%; laryngospasma; sore throat; bradycardia or hypotension defined as a decrease of at least 20% below the age-adjusted lower limit of heart rate or arterial blood pressure; tachycardia or hypertension defined as an increase of at least 20% above the age-adjusted upper limit of heart rate or arterial blood pressure; (8) satisfaction scores of bronchoscopists during the operation; (9) satisfaction scores of anesthesiologists; (10) satisfaction scores of parents 24 h after the operation. Given the age range of our study population (1–6 years), this score is reported as a proxy measure by the child’s parent or guardian, who is present throughout the preoperative, recovery, and immediate post-discharge periods. Satisfaction scores are measured subjectively by a simple numeric score between 1 (highly dissatisfied) and 10 (highly satisfied).

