### Data collection and management

Demographic data include sex, age, weight, height, and BMI. Baseline characteristics encompass ASA physical status, as well as baseline values for HR, NIBP, SpO_2_, and baseline cough frequency (“occasional” or “frequent but stable”). Periprocedural data include the following: the total number of coughing episodes during the FFB intervention period; procedure time; cumulative remifentanil dosage; success rate of the FFB operation; HR, NIBP, SpO_2_, PetCO_2_, body temperature, BIS value, severity grading of pneumonia; the usage and dosage of sugammadex, the corresponding TOF ratio at the time of reversal; cough scores recorded in the PACU; discharge time; and adverse events that occurs during the procedure and in the PACU, including desaturation (SpO_2_ < 90%), laryngospasm, sore throat, bradycardia or hypotension, tachycardia or hypertension. Additionally, the data will capture anesthesiologist satisfaction, bronchoscopist satisfaction and parent satisfaction. All raw data will be meticulously documented in the Case Report Forms (CRFs) by an independent investigator. Upon completion of the trial for all patients, the principal investigator and the data administrator will jointly verify the integrity and accuracy of the data. Subsequently, the data administrator will import the verified data into a designated electronic database and forward it to a statistician for final statistical analysis.

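### No single primary test is named: the outcome data choose the analysis, and the negative binomial branch is attached to a per-minute ratio without an exposure offset

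*Protocol article*

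**What the plan says.** The Primary endpoint section defines the outcome as cough frequency, "calculated as the total number of coughing episodes divided by the procedure time". It is a non-integer rate per minute.

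The Statistical analysis section then sets two layers of analysis, both steered by the observed data.

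- **Unadjusted.** "All data will be checked for normal distribution using the Kolmogorov test". Normal data go to the t-test; other data are "compared using the Mann-Whitney U test where appropriate".
- **Adjusted.** "If the primary endpoint adheres to a Poisson distribution or a negative binomial distribution, negative binomial regression is further utilized". The alternative is: "If the primary endpoint conforms to a normal distribution, a multiple linear regression model is further adopted". Both use the same covariates, and operation time is one of them. No offset or exposure term is mentioned, and no model is given for an endpoint that fits neither description.

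The section does not say whether the unadjusted test or the adjusted regression decides the trial.

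The ingredients of a count model are collected. Data collection and management lists "the total number of coughing episodes during the FFB intervention period", and Secondary endpoints has "procedure time defined as the duration from bronchoscope insertion to its removal".

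**The concern.** There are two linked problems.

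**The choice of analysis.** The effect measure could be a difference in means, a rank shift or a rate ratio, depending on a distribution check on the trial's own outcome. A treatment effect changes the shape of that outcome, so it also influences which analysis is run. Because the regression comes on top of the unadjusted test, two p-values will exist and neither is designated. The rule that conclusions are robust only if p < 0.05 under both alternative cough definitions has the same gap, since it does not say which p-value it means.

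**The negative binomial branch.** Poisson and negative binomial distributions describe integer counts, so a ratio cannot meet the stated condition. If the rate is modelled anyway, the model treats every child as observed for one time unit. It then takes its variance from a mean of 0.6 or less, although each rate averages many minutes. Operation time as an ordinary covariate does not repair this. Taken as the same quantity as procedure time (the article does not define it separately), operation time is also the endpoint's own denominator, is measured after randomisation, and is itself a secondary endpoint.

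**Working it through.** **Inputs from the Sample size section.** Control rate 0.6 to 0.89 per minute, SD 0.3, target 0.3 per minute, 64 per group, power 0.80, type I error 0.05. Two-sided testing is stated in the Statistical analysis section.

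**The plan's own figure.** n per group = 2(1.96 + 0.8416)²/d² = 15.70/d².
- 0.6 vs 0.3 with SD 0.3 gives d = 1 and n = 16 (17 with the t correction), so 64 is not reproduced.
- d = 0.5 gives 62.8, so 63 (64 with the t correction). With SD 0.3 that is, for example, 0.6 vs 0.45.

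This mismatch is a separate matter. It is used here only to show why 0.6 vs 0.45 is worth examining beside the stated target.

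**Assumptions.** The article gives no distribution of procedure time; the nearest hint is the subgroup cut "operation time (<20 min vs. ≥20 min"). Times are taken as lognormal with median 10 or 20 minutes. Counts are gamma-Poisson, with dispersion k chosen to match the stated SD:
- t = 10: √(0.6/10 + 0.083 × 0.6²) = 0.30
- t = 20: √(0.6/20 + 0.167 × 0.6²) = 0.30

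**Why the rate model fails.** Approximate analytic check, 64 per arm, 0.6 vs 0.45, time fixed at 10 minutes.
- Log rate ratio: ln(0.6/0.45) = 0.288.
- SE the model reports when the per-minute rate is the response (dispersion estimated at about zero): √[(1/0.6 + 1/0.45)/64] = 0.247.
- Actual SE: √[(1/6 + 0.083 + 1/4.5 + 0.083)/64] = 0.093. The reported SE is about 2.65 times too wide.
- Chance of significance: the estimate must exceed 1.96 × 0.247 = 0.483, and (0.483 − 0.288)/0.093 = 2.10, so about 0.018.
- With the count and offset: 0.288/0.093 − 1.96 = 1.13, so power about 0.87.
- Under no effect: reported SE 0.228, actual 0.088, so rejection needs a deviation of about 5.06 SE. Type I error is essentially zero.
- For 0.6 vs 0.3: ln 2 = 0.693, reported SE 0.280, actual 0.102. (1.96 × 0.280 − 0.693)/0.102 = −1.42, so power about 0.92.

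**Simulation.** 64 per arm; 2,000 runs under no effect, 800 at 0.6 vs 0.45, 400 at 0.6 vs 0.3. Operation time was the only covariate simulated. Ranges cover the two median times.

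| Analysis | Type I error | Power, 0.6 vs 0.45 | Power, 0.6 vs 0.3 |
|---|---|---|---|
| t-test | 0.050–0.051 | 0.85–0.88 | 1.00 |
| Mann-Whitney | 0.050–0.053 | 0.84–0.85 | 1.00 |
| Linear regression | 0.051–0.054 | 0.84–0.88 | 1.00 |
| Negative binomial on rate per minute, no offset | about 0 | 0.02 | 0.91–0.96 |
| Same, rate per hour | 0.055–0.056 | 0.85–0.88 | 1.00 |
| Negative binomial on count, log-time offset | 0.048–0.054 | 0.88–0.89 | 1.00 |
| Adjusted model chosen by normality check | 0.026–0.033 | 0.29–0.46 | 0.94–0.97 |
| Smallest p of five candidate tests | 0.074–0.076 | – | – |

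The five candidates in the last row are the t-test, Mann-Whitney, linear regression, and the negative binomial with the per-minute rate and with the offset. Changing minutes to hours moves the rate model's power from 0.02 to 0.85–0.88 on the same data.

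**The pretest.** A normality check of Kolmogorov type on the pooled rates let the data pass as normal in 43–59% of trials with no effect, 32–53% at 0.6 vs 0.45, and 8–19% at 0.6 vs 0.3. With no effect the branch is close to a coin toss, and the treatment effect shifts the odds.

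**Other runs.** Simulations with 70 per arm gave 2–5% power for the rate model at 0.6 vs 0.45, against 83–91% with the offset, and 94–98% at 0.6 vs 0.3. A further set (70 per arm, dispersion 0.15, mean 15 minutes) gave about 1% against 87% for a 25% reduction, 7.0% type I error for the better of Mann-Whitney and offset negative binomial, and 7.9% for the best of four tests.

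**The case against.** The strongest reply is that the condition itself implies a count. If a ratio cannot be negative binomial, the rate model never runs, and if the condition can be met, the variable must be the number of episodes. Count and time are both collected, and operation time is in the model, so a count model adjusted for time is a plausible reading. On that reading the missing offset costs almost nothing. With 70 per arm, dispersion 0.15 and median times of 10, 15 and 20 minutes, the count model with linear time gave type I error of 0.067, 0.060 and 0.061, against 0.064, 0.049 and 0.055 with the offset. Power for a 25% reduction was 0.82, 0.90 and 0.93, against 0.83, 0.91 and 0.94.

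This stands as far as it goes: the severe power loss belongs to one reading of the text. But the article defines the primary endpoint as the ratio and conditions the model on the primary endpoint, so the count reading must be supplied by the reader. If the branch never opens, a skewed rate is left with no adjusted model. A separate analysis plan may add detail, but the objection here is to a rule that the article states.

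A reader might also infer that the trial has no valid test at all, or that following the plan inflates false positives. The documents do not support either. The t-test, Mann-Whitney and linear model each hold about 5%; choosing between t-test and Mann-Whitney by the normality check gave 0.051–0.056; and the mis-specified branch errs towards missing an effect. The 7–8% figure requires picking the most favourable result, which the article does not plan but does not rule out.

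**Conclusion.** The point holds in this form: no one analysis is designated primary, the effect measure and p-value depend on a pretest of the outcome, and the count-model branch is conditioned on a variable that cannot satisfy it. If that branch is applied to the per-minute rate, the loss is severe for a moderate effect (power about 1–5% instead of about 83–91% at 0.6 vs 0.45) and small at the planned effect (about 91–98%), with type I error near zero. Under a count reading with time as a linear covariate, the loss is negligible.

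The sizes rest on assumed lognormal procedure times with median 10 to 20 minutes and on dispersion either matched to the stated SD of 0.3 or set at 0.15. The contradiction between endpoint and model, and the missing designation of a primary test, rest on the text alone.

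**What to change.** Name one primary analysis in advance: negative binomial regression of the episode count, log link, log(procedure time) as offset, with treatment and baseline covariates only, and one two-sided 5% test of the rate ratio with its 95% confidence interval. Remove operation time from the covariates, because it is measured after randomisation and is the endpoint's denominator. Drop the distribution pretest for the primary endpoint, and label the t-test or Mann-Whitney comparison of rates as supportive. State that the robustness rule for the alternative cough definitions refers to this same test.

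The cost is a change of wording, made before unblinding. Count and time are already collected, and no extra patients or visits are needed. In the simulation above, this analysis had type I error of 0.048–0.054 with 64 per arm.

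### Operation time, known only after randomisation and open to influence by coughing, is an adjustment covariate and a subgroup factor, and read literally procedure time is adjusted for itself

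*Protocol article*

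**What the plan says.** All references are to the protocol article.

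- **Statistical analysis, primary endpoint.** Negative binomial regression is planned, "adjusting for the influence of covariates [the severity classification of pneumonia, BMI, age, sex and operation time, baseline cough frequency" being the covariate list. If the endpoint is normally distributed, "a multiple linear regression model is further adopted for the same covariate adjustment".
- **Statistical analysis, secondary endpoints.** Logistic regression or a generalized linear model is used, "adjusting for the same covariates as those of the primary endpoint". No endpoint is excepted. A separate sentence assigns haemodynamics and PACU cough scores to a mixed linear model and names no covariates.
- **Statistical analysis, subgroups.** The list ends "and operation time (<20 min vs. ≥20 min").
- **Statistical analysis, opening paragraph.** Unadjusted two-group tests are also described, and the regressions come as a further step.
- **Secondary endpoints.** Item 5 is "procedure time defined as the duration from bronchoscope insertion to its removal".
- **Primary endpoint.** Cough frequency is "calculated as the total number of coughing episodes divided by the procedure time". An episode is "a period of continuous coughing that interferes with either adequate ventilation or procedural progress", and a deliberate halt in moving the bronchoscope counts as interference with progress.
- **Data collection and management.** Procedure time is listed with the periprocedural data, not with the baseline characteristics.

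**The concern.** A covariate in a randomised comparison should be fixed before treatment can influence it. Operation time is not. Study drug is given at induction, the laryngeal mask follows 60 s later, and only then is the bronchoscope inserted and the clock started. Some coughing episodes count precisely because they halt the procedure, so more coughing can mean a longer operation. If rocuronium reduces coughing, it may shorten the operation by that route.

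Three things are at stake:

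1. Adjusting cough frequency for operation time can remove part of the effect being estimated. It also makes the adjusted contrast one between children matched on something that happened after randomisation.
2. Applied without exception, the covariate list puts procedure time on both sides of its own model. Cumulative remifentanil is touched as well: the infusion runs throughout, so adjusting for duration closes one route by which rocuronium could lower the total dose.
3. The 20-minute strata may be filled partly according to how much each child coughed, so the arms within a stratum need not be comparable.

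**Working it through.** **Is it post-randomisation?** Yes. The order is randomisation, study drug, laryngeal mask, bronchoscope insertion (start of procedure time), bronchoscope removal (end). No other definition of operation time is given. A different one would still be post-randomisation.

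**Procedure time adjusted for itself.** The linear model is T = a + b·arm + c·T + other terms. Least squares reaches zero residual at a = 0, b = 0, c = 1, so b = 0 whatever the truth. In a numerical example with 70 per arm, the unadjusted difference was −3.5 min and the adjusted coefficient was 0. The exact zero is for an identity link. With another link the fit need not be exact, but the coefficient still does not estimate an effect on duration.

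**Primary endpoint.** The plan gives no figure of its own to reproduce here: neither a mean procedure time nor the time lost per episode is stated. From the Sample size section I take 0.6 episodes/min in controls and 0.3 with rocuronium (true ratio 0.50). The remaining inputs are assumptions:

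- T = cough-free time + p × episodes, with p the minutes lost per episode.
- Set-up A: 70 per arm, lognormal cough-free time with mean 15 min, dispersion 0.15, 400 trials.
- Set-up B: 70 per arm, cough-free time with median 18 min and log-SD 0.3, frailty variance 0.25, 600 trials.
- Set-up C: as A but with 64 per arm. C* raises the generating rates so that the observed control rate is near 0.6/min.

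The rate ratio comes from a cough-count model with a log-time offset:

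| p (min) | Set-up | Without covariate | With covariate | Shift |
|---|---|---|---|---|
| 0 | B | 0.502 | 0.502 | 0 |
| 0.1 | B | 0.524 | 0.525 | 0.001 |
| 0.25 | A | 0.541 | 0.546 | 0.005 |
| 0.25 | B | 0.545 | 0.558 | 0.013 |
| 0.25 | C | 0.539 | 0.548 | 0.009 |
| 0.5 | A | 0.569 | 0.589 | 0.020 |
| 0.5 | B | 0.576 | 0.611 | 0.035 |
| 0.5 | C | 0.569 | 0.596 | 0.027 |
| 0.5 | C* | 0.593 | 0.633 | 0.040 |

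In the linear model at p = 0.5, the rate difference goes from −0.191 to −0.176 in A (0.015/0.191 = 8%) and from −0.186 to −0.164 in B (0.022/0.186 = 12%).

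The move from 0.50 to the *without covariate* column is not due to the covariate. It arises because pauses enlarge the denominator. Ignoring between-child variation, the observed rate is λ/(1 + λp). At p = 0.5 that is 0.6/1.30 = 0.462 against 0.3/1.15 = 0.261, a ratio of 0.565.

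A pause of 1 min in set-up A gives 0.617 to 0.664. I do not rest on it: at an observed 0.6 episodes/min, 0.6 × 1 = 60% of the procedure would be pause.

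**The 20-minute subgroup (set-up B).** The same ratio of 0.50 was built in for every child:

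| p (min) | Rocuronium children under 20 min | Control children under 20 min | Rate difference, <20 min | Rate difference, ≥20 min |
|---|---|---|---|---|
| 0 | 63% | 63% | −0.298 | −0.302 |
| 0.1 | 60% | 56% | −0.250 | −0.283 |
| 0.25 | 54% | 46% | −0.195 | −0.251 |
| 0.5 | 46% | 32% | −0.135 | −0.198 |

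Once coughing adds time, the strata are filled unequally by arm, and the rate difference varies by stratum although no such variation was built in.

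**The case against.** **Time is needed as exposure.** It is, but an offset does that. The text calls operation time a covariate and names no offset. An offset has no role in a linear model of a rate already divided by time.

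**Unadjusted tests survive.** This stands. A reader might infer that the covariate breaks the randomised comparison altogether. The documents do not support that: unadjusted tests are described first, and the problem lies in the adjusted models. The plan does not say which result is decisive.

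**Not every endpoint is affected.** This also stands. The mixed-model sentence names no covariates, so haemodynamics and PACU cough scores may be exempt.

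**Rocuronium is not shown to shorten the procedure.** Correct. The hypotheses in the abstract and Introduction do not list shorter procedures, and some episodes count only because they disturb ventilation. What the documents support is that duration can be affected.

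**No analyst would regress procedure time on itself.** Probably not, and the Discussion plans a plain group comparison of it. A reader might infer that a false null will be published. It is more likely a blanket phrase that needs an exception, but as written it gives none.

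**The bias is small and conservative.** In these scenarios, yes. In set-up C with pauses of 0.1 to 0.5 min, and in C*, every simulated trial stayed significant with the covariate. Power fell noticeably, to 0.88, only in the recalibrated 1-min case. Nothing here suggests a manufactured positive result.

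**The time subgroup has a clinical motive.** The Discussion notes that some operations outlast rocuronium's action. That explains the interest but does not make the strata comparable between arms.

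**Conclusion.** The point holds in limited form. The plan conditions the adjusted primary models, and the secondary endpoints modelled by logistic regression or a generalized linear model, on a variable that it also treats as an outcome and that coughing can lengthen.

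The firmest consequence needs no assumption about pause length: read literally, and taking operation time to be procedure time, the adjusted linear model for secondary endpoint 5 returns zero whatever the truth.

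For the primary endpoint the size is uncertain because it depends on time lost per episode, which the documents do not give. The covariate introduces no bias if that time is nil. It moves the rate ratio towards the null by about 0.005 to 0.013 at 0.25 min and 0.02 to 0.04 at 0.5 min. The 20-minute subgroup is open to the same selection.

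**What to change.** 1. Delete operation time from the covariate list of all primary and secondary models.
2. Model the number of coughing episodes as the count, with log procedure time entering only as the offset.
3. Drop the 20-minute subgroup, or keep it labelled as exploratory and non-randomised. The operation-type subgroup already planned offers a pre-procedure factor, provided it is taken as scheduled, so no new subgroup is needed.

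An analysis of coughing by elapsed time would not be a wording-only substitute. The Data collection section lists only the total number of episodes, so time-stamped events would have to be recorded.

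The three changes are to wording and are best made before unblinding. The price is slightly less variance explained in the adjusted models. They leave untouched the dilution caused by counting pause time in the denominator, which belongs to the endpoint definition.
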